### Trial design {8}

DRIFT is designed as a two-arm randomized controlled trial. Eligible participants will be randomized into one of two study arms: IMF or DCR. This study was powered as a superiority trial. However, if superiority cannot be established, power was also performed for non-inferiority, a priori (see item 14). There are no planned interim analyses. Outcome measures will take place at baseline and weeks, 13, 26, 39, and 52. Selected follow-up measures obtained 26 weeks after completion of the 52-week intervention (i.e., week 78) were added via a protocol amendment after study start. This is not a primary study outcome timepoint, but rather a 26-week post-primary outcome follow-up.

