### Sample size {14}

An a priori power calculation was performed for the primary outcome (weight) using nQuery 7.0 (Statistical Solutions Ltd, Cork, Ireland). In our power analyses, we made the following assumptions: (1) power ≥ 0.90 and above for the primary outcome is ideal; (2) the significance level under the null hypothesis will be set at *α* = 0.05; (3) null hypotheses will be tested against two-directional (that is, two-tailed) alternative hypotheses; (4) a 3-kg between-group difference in weight loss was deemed the minimum difference of clinical importance; and (5) the primary analysis will use the intent-to-treat principle in which all randomized participants are analyzed. We will enroll 150 participants (75 participants per randomized group) to provide 90% power at 5% significance to detect a between-group difference of 3 kg in body weight at 52 weeks. With an attrition rate of as high as 20%, we retain 82% power in a sensitivity (completer’s) analysis. Standard deviation (SD) of weight loss used in this calculation was 5.6 kg and was based on a 52-week interventional study using the Colorado Weigh program conducted at our research center [96]. There are no previous data for us to estimate the effect size for any of the outcomes at 52 weeks. If superiority of IMF to DCR cannot be established, we will perform a non-inferiority test using 2.26-kg weight loss as a non-inferiority margin. In this case, we would have 79% power to establish non-inferiority of IMF as compared to DCR assuming no difference in effect of weight loss between the two groups.

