### Statistical methods

#### Statistical methods for primary and secondary outcomes {20a}

Baseline characteristics will be summarized by treatment groups using descriptive statistics. Normality assumptions will be evaluated, and transformations used (e.g., square root and log) as appropriate. Body weight is the primary outcome variable and others are secondary or exploratory outcomes. Consequently, no adjustment for multiple outcomes will be applied. *P*-values < 0.05 will be considered significant. Any imbalance in baseline characteristics between groups that could potentially be a confounding factor for the outcome will be adjusted for in the statistical model.

The primary analysis will use the “intent-to-treat” principle and all randomized participants will be analyzed. Each continuous outcome will be analyzed using a linear mixed effects model. The fixed effects of the linear mixed effects model will consist of treatment group (IMF or DCR) and time of measurement (i.e., baseline and follow-up time points) and their interaction. Time of measurement will be treated as a continuous or categorical variable, as appropriate. Test of the interaction assesses the difference in post-intervention change from baseline between two groups and is used to quantify the effectiveness of the intervention. The 90% confidence interval for the interaction will be calculated. Incidence of adverse events, protocol modifications, and attrition will be compared between groups using chi square or Fisher’s exact test as appropriate.

To explore the impact of selected biologic, psychosocial, behavioral, and/or environmental variables on the intervention effect, we will initially apply models similar to those being tested in aim 1, with the addition of a potential effect moderator as a covariate and its interaction term (i.e., intervention × moderator × time interaction) in addition to related two-way interaction terms. Among factors with a significant three-level interaction, we will further use post-intervention weight loss as the outcome and multiple linear regression to examine their association with the outcome and its interaction with intervention. Similar multiple logistic regression analysis will also be conducted with the outcome dichotomized as responder and non-responder using clinical criteria.

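### The confidence interval named for the treatment effect is 90%, unrestricted, while superiority is tested at two-sided 5%; the 95% interval should accompany that test and the 90% interval be tied to the weight non-inferiority comparison

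*Protocol article*

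**What the plan says.** On the test, the article is clear and consistent.

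- Trial design {8}: "This study was powered as a superiority trial". The next sentence adds that power for non-inferiority was also worked out in advance, for use if superiority is not shown.
- Sample size {14}: "the significance level under the null hypothesis will be set at" 0.05, and "null hypotheses will be tested against two-directional (that is, two-tailed) alternative hypotheses". The enrolment target follows from this: "We will enroll 150 participants (75 participants per randomized group) to provide 90% power at 5% significance" for a 3 kg difference, with an SD of 5.6 kg. The fallback non-inferiority test has a margin of 2.26 kg and a stated power of 79% at no true difference. No significance level or sidedness is attached to it.
- Statistical methods {20a}: p-"values < 0.05 will be considered significant".

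On the estimate, the same statistical section says "Each continuous outcome will be analyzed using a linear mixed effects model", and of the group-by-time term: "Test of the interaction assesses the difference in post-intervention change from baseline between two groups and is used to quantify the effectiveness of the intervention". Directly after that comes the interval sentence, "The 90% confidence interval for the interaction will be calculated". It mentions neither non-inferiority nor weight.

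**The concern.** A two-sided 5% test corresponds to a 95% interval: the test rejects exactly when the interval excludes zero. A 90% interval corresponds to a two-sided 10% test, or to a one-sided 5% test against a margin. The article tests the interaction at the first level and gives an interval at the second, without saying that the interval serves a different question.

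At stake is how the results will read. For any outcome with p between 0.05 and 0.10, the results table would show an interval that excludes zero beside a test declared not significant. For weight, a reader can at least guess that the 90% interval relates to non-inferiority. For body composition, metabolic measures, energy intake and physical activity there is no non-inferiority test, so a 90% interval has no stated purpose.

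**Working it through.** **Inputs** (Sample size {14}): 75 per arm, SD 5.6 kg, superiority difference 3 kg, two-sided 5%, non-inferiority margin 2.26 kg, true difference 0 for non-inferiority, attrition up to 20%.

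**Planning standard error.** SE = SD × √(2/n) = 5.6 × √(2/75) = 0.914 kg.

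**Step 1: the plan's superiority power.** 3 / 0.914 = 3.28, and 3.28 − 1.960 = 1.32. This gives 90.7% (normal approximation); the noncentral t gives 90.3%. The stated 90% reproduces, so two-sided 5% is the level that was used.

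**Step 2: the plan's non-inferiority power.** 2.26 / 0.914 = 2.47.

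| Level assumed | Normal approximation | Noncentral t | Stated |
|---|---|---|---|
| One-sided 5% | 2.47 − 1.645 = 0.83, giving 79.6% | 79.3% | 79% |
| One-sided 2.5% | 2.47 − 1.960 = 0.51, giving 69.5% | 69.0% | 79% |

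Only one-sided 5% reproduces the stated figure. A two-sided 90% interval is the one that carries out a one-sided 5% non-inferiority test, so the 90% level fits that test.

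**Step 3: interval half-widths**, using t with 148 degrees of freedom.

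- 90%: 1.655 × 0.914 = 1.51 kg
- 95%: 1.976 × 0.914 = 1.81 kg

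(The normal approximation gives 1.50 and 1.79 kg. With 60 per arm, that is at 20% attrition, SE = 1.022 kg and the t-based half-widths are 1.70 and 2.02 kg.)

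**Step 4: where interval and test part.** An observed difference between 1.51 and 1.81 kg gives a 90% interval that excludes zero and a p-value above 0.05. Take 1.60 kg: 1.60 / 0.914 = 1.75, which lies between 1.655 and 1.976, so p is between 0.05 and 0.10. The 90% interval is 1.60 ± 1.51, or 0.09 to 3.11 kg. The 95% interval is 1.60 ± 1.81, or −0.21 to 3.41 kg.

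**Step 5: how often this would happen for weight** (75 per arm, SD 5.6 kg, normal approximation).

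| True difference (kg) | Chance that p is between 0.05 and 0.10 |
|---|---|
| 0 | 5.0% |
| 1 | 10.0% |
| 1.5 | 12.4% |
| 2 | 11.6% |
| 3 | 4.2% |

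The 5.0% at no true difference does not depend on the SD or sample size, so it applies to each secondary outcome as well.

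**The case against.** The strongest reply is that nothing in the decision rule depends on this interval. The article names the test of the interaction as the assessment of the difference, sets p below 0.05 as the criterion, and gives the interval as a separate summary. An outcome with p between 0.05 and 0.10 is not significant under the plan, whatever interval is printed beside it. The 90% level also has a sensible use in this trial, as step 2 shows, and is probably deliberate. Both replies stand.

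Two stronger readings are therefore not supported.

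- A reader might infer that the plan tests superiority at 10%. It does not: only someone who ignored the stated p-value rule and judged superiority from the interval would be working at that level.
- A reader might infer that precision is overstated, or that the interval is too narrow. A 90% interval labelled as 90% has its nominal coverage; it is narrower than a 95% interval because it claims less.

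It can also be said that confidence levels are detail that an article may leave to an analysis plan not seen here, that the article never says the 90% interval is the only one to be reported, and that the interval sentence speaks of the interaction in the singular. This has some weight, but it does not dispose of the point. The article did not stay silent: it chose a level and attached it, without restriction, to the term that quantifies effectiveness, in a paragraph whose model covers every continuous outcome. Reading it as the weight non-inferiority interval requires working back from the power figure, because no significance level is given for that test and the sentence does not mention it.

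**Conclusion.** The point holds as a mismatch between the planned interval and the planned test. It affects reporting and interpretation; the superiority decision, its type I error, its power and the sample size are untouched. At the planning standard error, the mismatch covers observed weight differences between about 1.51 and 1.81 kg. It would arise in 4% to 12% of trials over the true differences examined (0 to 3 kg).

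The kilogram figures assume 75 per arm, an SD of 5.6 kg and a simple comparison of mean changes. The mixed model's standard error will differ and the limits will move with it. The disagreement when p lies between 0.05 and 0.10 does not depend on those assumptions. That the 90% level was meant for non-inferiority is an inference from the 79% power, not something the article states.

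**What to change.** Replace the interval sentence in Statistical methods {20a}, or settle it in the analysis plan, so that it says:

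1. The between-group difference in change is reported with a 95% confidence interval, matching the two-sided 5% test, for the week-52 weight contrast and for all secondary continuous outcomes.
2. A 90% confidence interval is reported in addition, for weight only, as the interval for the non-inferiority comparison at one-sided 5% with the 2.26 kg margin.

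The second sentence also puts on record the level that the 79% power implies. The cost is one or two sentences; no data, sample size or model changes.

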### Objectives {7}

The aims of DRIFT are to (1) compare changes in body weight (primary outcome), body composition, and metabolic parameters induced by IMF and DCR; (2) evaluate the impact of IMF vs. DCR on EI and dietary adherence; and (3) evaluate the impact of IMF vs. DCR on energy expenditure (EE) and patterns of PA. Informed by our prior IMF pilot study that suggested that IMF may be better for long-term weight loss maintenance vs. DCR [15], our a priori hypotheses are that IMF will generate greater weight loss (primary outcome), greater decreases in fat mass, improved maintenance of lean mass, and greater improvements in metabolic parameters (fasting lipids, insulin sensitivity, blood pressure) at 52 weeks. While these hypotheses are contrary to recently published data from long-term studies, these data were not available at the time the study was designed. We also will use the National Institutes of Health (NIH) Accumulating Data to Optimally Predict obesity Treatment (ADOPT) framework to evaluate selected biologic, behavioral, environmental, and psychosocial predictors of weight loss response [24–28].

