#### Metabolic/hormonal evaluations

A 12-h fasting blood sample will be obtained for assessment of glucose, insulin, hemoglobin A1c, lipid panel, leptin, ghrelin, peptide YY, and highly sensitive C-reactive protein (hs-CRP) at baseline and weeks 26, 52, and 78. Circulating nutrients and hormonal regulators of fuel metabolism (glucose, insulin, triglycerides, free fatty acids, beta-hydroxybutyrate, and cortisol) will be measured at baseline after both a fed (i.e., 12-h fast) and fast day (i.e., 36-h test fast day with 500 kcal/day (women) or 600 kcal/day (men)) to assess if baseline metabolic response to fasting can serve as a predictor of weight loss. Labs will be analyzed by the UCHealth Clinical Laboratory (beta-hydroxybutyrate) or the Clinical Translational Research Institute (CTRC, all other labs). Insulin sensitivity (homeostasis model assessment of insulin resistance, HOMA-IR) will be calculated as ([insulin] × [fasting glucose × 0.055]/22.5).

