#### Psychosocial, behavioral, and environmental predictors of response

To measure psychosocial, behavioral, and environmental constructs which may predict weight loss response, several validated questionnaires and computer-based tasks will be administered to participants. Selection of measures was informed by the recommendations of the NIH ADOPT Core Measures Project [24, 27, 28]. Questionnaires will be administered at baseline and at weeks 13, 26, 52, and 78 (see Table 4). Each month, participants will also be asked to report any changes in their home or work address, to capture changes in their built, social, and community food environments.

**Table 4 Tab4:** Psychosocial, behavioral, and environmental constructs by study week

		Timepoint (week)				
Questionnaire	Construct measured	0	13	26	52	78

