DRIFT will fill this gap in the literature by examining the effectiveness of IMF as a dietary strategy to achieve weight loss compared to DCR, the current standard-of-care, within the context of a 52-week, guideline-based behavioral support program for obesity treatment. We will use objective methods to measure EI (DLW intake-balance method) and PA (activPAL device) to allow for an accurate comparison of adherence to the dietary and PA prescriptions between the IMF and DCR groups. This trial is also unique in that it will be one of the first obesity treatment trials to implement the recommendations from the NIH ADOPT framework to evaluate selected biologic, behavioral, environmental, and psychosocial predictors of weight loss response [24–28]. Our findings may have significant public health implications as this study will generate robust data regarding long-term weight loss effectiveness of IMF as compared to DCR. We anticipate that results will further our understanding of the impact of IMF on energy balance and will provide preliminary insight into predictors of weight loss response within IMF and DCR.

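### The regression of weight loss on candidate predictors is reserved for factors with a significant intervention × moderator × time term, so a factor that predicts to a similar degree in both arms passes only about 5% of the time

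*Protocol article*

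**What the plan says.** Four places in the protocol article describe the purpose as prediction of weight loss:

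- Objectives {7}: the trial will "evaluate selected biologic, behavioral, environmental, and psychosocial predictors of weight loss response".
- Metabolic/hormonal evaluations: fed-day and fast-day bloods are taken at baseline "to assess if baseline metabolic response to fasting can serve as a predictor of weight loss".
- Psychosocial, behavioral, and environmental predictors of response: questionnaires and tasks are given to capture "psychosocial, behavioral, and environmental constructs which may predict weight loss response".
- Discussion: the results "will provide preliminary insight into predictors of weight loss response within IMF and DCR".

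One place describes the analysis, Statistical methods for primary and secondary outcomes {20a}. It asks about the impact of these "variables on the intervention effect, we will initially apply models similar to those being tested in aim 1", adding each factor as a potential effect moderator with an "intervention × moderator × time interaction" and the related two-way terms. A restriction follows: "Among factors with a significant three-level interaction, we will further use post-intervention weight loss as the outcome and multiple linear regression to examine their association". The same sentence says that this regression also examines the factor's interaction with intervention. A similar logistic analysis of responders is then mentioned. The section's general threshold is p < 0.05.

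**The concern.** The objective and the gate have different null hypotheses. For a predictor, the null is no association between the factor and weight loss. For the three-way term, the null is that the association is the same in both arms. A factor strongly related to weight loss in IMF and DCR alike satisfies the second null exactly, so the plan does not take it forward to the regression that would show the association.

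The protocol collects a large baseline battery for this objective (Table 4) and describes the predictor work as a distinctive feature of the trial. Followed as written, the plan looks for effect modifiers, for which 75 per arm gives limited power. It has no stated step that would bring out a general predictor. The issue is which hypothesis the gate tests. It is separate from how many factors are screened or whether they are re-tested in the same data.

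**Working it through.** **Inputs.** From Sample size {14}: 75 per arm, 60 per arm after 20% attrition, SD of weight loss 5.6 kg, two-sided 5%. The protocol gives no correlation between any factor and weight loss, so the values of r below are assumptions shown over a range.

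**The plan's own figure.** The protocol states no power for the predictor analysis. Its primary power does reproduce. The standard error is 5.6 × √(2/75) = 0.914 kg, 3/0.914 = 3.28, and Φ(3.28 − 1.96) = 90.7% (90.3% with the t distribution), against the stated 90%. With 60 per arm it is 83.5% (82.9% with t), against the stated 82%.

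**The model.** Let Y be weight change at week 52, G the arm and M the standardised factor:

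Y = β₀ + β₁G + β₂M + β₃GM + error.

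With complete data and time taken as baseline versus week 52, β₃ is the three-way term and β₂ is the moderator × time term in the reference arm. The gate tests β₃ = 0. If the factor has the same slope in both arms, β₃ = 0 whatever the size of β₂. The pass rate is then the test's type I error, 5%. This follows from the model and needs no simulation.

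**Direct test of association, adjusted for arm, equal r in both arms.** The noncentrality is approximately r√N/√(1 − r²); the SD cancels.

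- r = 0.2, N = 150: 0.2 × 12.25/0.980 = 2.50, and Φ(2.50 − 1.96) ≈ 71%.
- r = 0.3, N = 150: 0.3 × 12.25/0.954 = 3.85, and Φ(3.85 − 1.96) ≈ 97%.

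**Gate with unequal slopes.** The noncentrality is approximately (r₂ − r₁)/√[(1 − r₁² + 1 − r₂²)/n].

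- 0.2 against 0.4, n = 75: 0.2/√(1.80/75) = 0.2/0.155 = 1.29, so about 25% pass.
- 0.1 against 0.4, n = 75: 0.3/√(1.83/75) = 0.3/0.156 = 1.92, so about 48% pass.

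**Simulation** (8,000 trials per row, SD 5.6 kg), which agrees with these approximations:

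| r in the two arms | Per arm | Passes gate | Direct test finds it |
|---|---|---|---|
| 0.2 / 0.2 | 75 | 5.4% | 70% |
| 0.3 / 0.3 | 75 | 4.8% | 97% |
| 0.4 / 0.4 | 75 | 4.9% | 99.9% |
| 0.2 / 0.2 | 60 | 4.8% | 60% |
| 0.3 / 0.3 | 60 | 5.0% | 92% |
| 0.2 / 0.4 | 75 | 24% | 97% |
| 0.3 / 0.5 | 75 | 26% | 99.9% |
| 0.1 / 0.4 | 75 | 47% | 87% |

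The last three rows mean that 76%, 74% and 53% are dropped; with 60 per arm the figures are 80%, 78% and 62%.

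**Repeated-measures version.** A joint 4-degree-of-freedom gate over weeks 13, 26, 39 and 52 (3,000 trials, assumed covariance) passes an equal-slope factor 5.0% to 5.5% of the time for r = 0.2 to 0.4. Using all visits does not change the result.

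**The case against.** The strongest defence is that the gate suits the question its own paragraph asks. That paragraph concerns influence on the intervention effect and calls each factor a potential moderator, and a three-way interaction is the right test for that. This stands for the moderator question. It does not cover the predictor question in the objectives, the measurement sections and the Discussion. Even the Discussion's reference to prediction within each arm asks for within-arm association, not a difference between arms.

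A second defence is that the first-stage model, fitted for every selected factor, already contains moderator × time, so the association is estimated before any gate. This is true, and it rules out saying that the association is never estimated. But no test, decision or report is attached to that term, and the stated association regression is kept for factors that pass. An unseen analysis plan might fill the gap, yet the gate is explicit here: a plan that follows it inherits the fault, and one that does not departs from the protocol.

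Four stronger readings are tempting and are not supported:

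- A reader might infer that any factor predicting in both arms is almost always discarded. About 95% applies only to similar slopes.
- A reader might infer that the logistic analysis is explicitly gated. It is described only as similar, so the gate is a natural reading and not a statement.
- A reader might infer that predictors are a main aim. Objectives {7} numbers three aims and adds the predictors afterwards, unnumbered; the methods call the work exploratory and the Discussion promises only preliminary insight.
- A reader might infer that factors failing the gate will be declared non-predictive. The protocol says only that those passing are examined further.

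The gap between 5% and 70% or 97% also compares tests of two different hypotheses. It measures how poorly the gate serves the predictor question, not a defect in the interaction test.

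**Conclusion.** The point holds as a mismatch between an exploratory objective and the analysis fixed for it. For factors with similar slopes in the two arms, the 5% pass rate is a property of the test and rests on no assumed correlation. The detection rates it is set against (about 70% at r = 0.2 and 97% at r = 0.3 with 75 per arm; 60% and 92% with 60) rest on assumed correlations and a linear relation. With clearly unequal slopes, 53% to 76% are dropped at 75 per arm in the cases tried. The text should be changed, because following it gives a worse answer to the stated predictor question. The primary and secondary comparisons between arms do not depend on it.

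**What to change.** In Statistical methods {20a}:

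1. Delete the clause that makes a significant three-way interaction the condition for the association regressions, and say whether the logistic responder analysis is likewise ungated.
2. For every pre-selected baseline factor, estimate its association with week-52 weight change from the moderator × time term at week 52, with arm and arm × time in the model. Report pooled and within-arm estimates with confidence intervals, labelled exploratory.
3. Keep the intervention × moderator × time contrast as a separate exploratory analysis of effect modification.

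The cost is a wording change and extra models on data already collected, with no added participants, visits or measurements. The small downside is a larger number of exploratory estimates to report and label as such.

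### Exploratory moderators picked by an unadjusted p < 0.05 interaction test are re-tested in the same participants, so the second stage exaggerates their effects and cannot corroborate the first

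*Protocol article*

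**What the plan says.** The moderator analysis is in the protocol article under Statistical methods for primary and secondary outcomes {20a}. Its purpose is exploratory: "To explore the impact of selected biologic, psychosocial, behavioral, and/or environmental variables on the intervention effect". It has three steps.

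1. A mixed model like the one for the main aim, "with the addition of a potential effect moderator as a covariate and its interaction term (i.e., intervention × moderator × time interaction"), plus the related two-way terms.
2. A regression restricted by the result of step 1: "Among factors with a significant three-level interaction, we will further use post-intervention weight loss as the outcome and multiple linear regression". This examines each factor's association with weight loss and its interaction with intervention.
3. "Similar multiple logistic regression analysis will also be conducted with the outcome dichotomized as responder and non-responder using clinical criteria".

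The section gives one significance rule: P-"values < 0.05 will be considered significant". Sample size {14} makes the tests two-sided. The only statement on multiplicity is "Consequently, no adjustment for multiple outcomes will be applied", which follows from body weight being the single primary outcome and concerns outcomes, not moderators.

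The candidate pool is described under Psychosocial, behavioral, and environmental predictors of response, where "several validated questionnaires and computer-based tasks will be administered to participants" and Table 4 lists them. Neither place says which of them, or how many, enter step 1.

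**The concern.** Step 2 takes only factors that have already shown a significant interaction with arm and estimates that interaction again on the same people's weight loss. Step 3 does so once more on a dichotomised form of the same outcome. A factor selected by chance brings its chance pattern into every later model. The later estimates are conditioned on a large observed effect, and their p-values do not have a 5% false-positive rate for the factors that reach them.

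At stake is how the predictor results are read. Evaluating predictors of response is among the objectives {7}, and the Discussion expects preliminary findings on them for both arms. Agreement between a mixed, a linear and a logistic model could look like three pieces of evidence when it is largely one set of noise seen three times.

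**Working it through.** **Inputs.** 150 participants, 75 per arm; SD of weight loss 5.6 kg; minimum important difference 3 kg; two-sided 0.05 (all Sample size {14}). The protocol gives no number of tests, error rate or power for the moderator analysis.

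**Plan's own figure.** SE of the arm difference = 5.6 × √(2/75) = 0.914 kg. Power ≈ Φ(3/0.914 − 1.96) = Φ(1.32) = 0.907 (0.903 with the noncentral t). The stated 90% is reproduced, so the SE can be used below.

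**Candidate pool.** Rows of Table 4 marked at week 0: 26 psychosocial + 6 behavioral + 2 environmental = 34, one of them optional. This is what is collected. Some rows hold several scores, and the biologic markers are outside the count.

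**Stage 1.** For k independent tests with no true moderator, P(at least one false positive) = 1 − 0.95^k, and the expected number is 0.05k.

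| k | P(at least one) | Expected |
|---|---|---|
| 5 | 22.6% | 0.25 |
| 10 | 40.1% | 0.5 |
| 20 | 64.2% | 1.0 |
| 34 | 82.5% | 1.7 |

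Reaching 95% takes 59 independent tests, and reaching 99% takes 90.

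**Stage 2 on the same data.** A null simulation used n = 150 and 1,000 runs, with k standardised moderators sharing a common correlation ρ. Change at weeks 13, 26, 39 and 52 was a person-specific slope (SD 5.0 kg per 52 weeks) plus visit noise (SD 2.0 kg), so the week-52 SD is √(25 + 4) = 5.4 kg, near the plan's 5.6. Stage 1 tested moderator × arm on the fitted slope, as a stand-in for the three-way test with continuous time. Stage 2 tested moderator × arm on week-52 change. For k = 34:

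| ρ | Any at stage 1 | Any at both stages | Re-significant, given selected |
|---|---|---|---|
| 0 | 83.5% | 74.5% | 75% |
| 0.3 | 69.9% | 60.8% | 77% |
| 0.5 | 53.7% | 45.4% | 76% |

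The mean number falsely selected stayed at about 1.7 throughout. With k = 10 the re-significance rate was 73–78%, so it hardly depends on how many moderators are screened. An independent check would give 5%.

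The cause is overlap of the two outcomes. With times t = 0.25, 0.5, 0.75, 1, Σt² = 1.875. The slope has variance 25 + 4/1.875 = 27.1, and its covariance with week-52 change is also 27.1. The correlation is √(27.1/29) = 0.97.

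**Size of the exaggeration.** For a standardised moderator, the SE of the arm difference in slope on week-52 change is about √(2 × 5.6²/75) = 0.91 kg per SD. Significance needs about 1.96 × 0.91 = 1.8 kg per SD. For a null moderator, the mean |z| given |z| > 1.96 is φ(1.96)/0.025 = 0.0584/0.025 = 2.34, so one that passes shows on average 2.34 × 0.91 = 2.1 kg per SD. Between people 1 SD above and 1 SD below the mean, that is a spurious difference in treatment effect of about 4.3 kg, against the plan's 3 kg. This assumes selection and estimation on the same week-52 contrast, with no attrition.

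**The case against.** The protocol presents this as exploration, and its Discussion calls the expected insight preliminary. It never says the second stage confirms the first; the regression is there to describe the flagged factors. A moderator list and error control for exploratory tests are commonly left to an analysis plan, which is not at hand. The sentence waiving adjustment is about outcomes and is not offered as a reason for leaving moderators unadjusted.

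All of this stands and limits the weight of the point. The missing list is not the complaint, and an unadjusted exploratory screen is not in itself an error. What remains is a rule that the protocol does fix: significance decides which factors are estimated again in the same data. An exploratory label does not remove the bias in those estimates.

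A reader might infer that all 34 baseline instruments are screened and that false predictors are nearly certain. The text does not support this. It speaks of a selection of variables, most instruments are also repeated at later visits for other uses, and several scales plainly overlap in construct. Even 34 independent tests give 82.5%; correlation or a shorter list lowers it. Separate testing of subscales and biologic markers could raise it, but the protocol does not say this is done.

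**Conclusion.** The point holds in a limited form. The second-stage interaction estimates are biased away from zero and their p-values cannot support the first stage, whatever the number of moderators. In the simulation about three quarters of falsely selected factors were significant again. That figure rests on the assumed visit variances and on continuous time in stage 1; a weaker overlap between the two outcomes would lower it.

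The chance of at least one false moderator is conditional on an unstated number of tests: about 23% for 5, 40% for 10 and 82.5% for all 34 if independent and null, or about 54–70% for 34 scales correlated at 0.5–0.3. The analysis is exploratory and the primary outcome is unaffected. This is a cheap improvement, not an error that threatens the trial's main conclusion.

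**What to change.** For every moderator screened, report the arm-by-moderator estimate at week 52 with its confidence interval, whether or not it is significant, and give Benjamini-Hochberg adjusted values across that set. With independent tests and no true moderator, flagging at an adjusted 0.05 holds the chance of any false flag at 5%, in place of the 23–82.5% above.

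Drop the significance-filtered linear and logistic re-tests, or keep them as description only, without p-values and with a note that the factors were selected in the same data. One shrunken joint model on continuous weight change is an option, not a requirement.

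The cost is a change of wording and modest programming, with no new data and no change to the primary analysis. The downside is fewer nominally significant exploratory findings.
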